#### Data monitoring

2.8.4

There is no data monitoring committee designated to this trial. Any adverse and serious adverse events will be immediately reported to the principal investigator and the primary sponsor.

### Ethics and dissemination

2.9

#### Research ethics approval

2.9.1

This study follows the Declaration of Helsinki on medical protocols and ethics; all documents of the trial have been approved by the local Ethics Committee of Federal State Autonomous Educational Institution of Higher Education I.M. Sechenov First Moscow State Medical University of the Ministry of Health of the Russian Federation (Sechenov University) (reference no. 10–19).

#### Protocol amendments

2.9.2

Any protocol amendments that may influence the conduct of the study, will be communicated to the local ethics committee and study director, and will be uploaded to clinical trials.

#### Consent or assent

2.9.3

A member of the research team will obtain the consent form. All participants will be able to address their questions about the study to 1 of the members of the research team. Consent form is described in Supplemental Digital Content (Appendix 1).

#### Confidentiality

2.9.4

All patient data will be secured at the study site. No one apart from the members of the research team will have access to any patient data, including anonymized eCRFs with a coded ID, as well as filled out questionnaires.

#### Access to data

2.9.5

No one apart from the members of the research team will have access to the final trial dataset.

#### Dissemination policy

2.9.6

Trial results will be e-mailed to all participants of the trial. Trial results will be disseminated to healthcare professionals via publication in a peer-reviewed scientific journal and by mass media, as well as conference papers to inform the public and stakeholders, and will be uploaded to the primary registry. We have no intention of granting public access to the full protocol, participant-level dataset, and statistical code.

## Discussion

3

The results of this RCT may demonstrate the absence of significant advantages in Doppler guidance technology for hemorrhoidal arteries detection in HAL-RAR procedures compared with the simple and accessible to any surgeon finger-guided hemorrhoidal arteries detection concerning the efficiency in eliminating hemorrhoidal prolapse and/or hemorrhoidal bleeding. We will analyze frequency of postoperative complications, the intensity of the pain syndrome, the relapse rate, and individual QOL level. It will allow us to conclude whether the HAL-RAR with finger hemorrhoidal artery detection is effective and safety procedure for hemorrhoids disease treatment.

The design of this study has certain limitations. Firstly, there is quite often mismatching of doctors regarding the stage of the HD as well as stage of each hemorrhoidal pile. So the group might be heterogenic regarding the preoperative stage of the HD.

Another issue is the uncertainty of the definition of HD recurrence after surgery. In this protocol, we determined it as appearance of any new symptoms of HD or persistence of previous ones. But we suppose that nevertheless procedure might be effective for preoperatively existed symptoms new ones might appear. So we will try to figure out the difference of preexisting symptoms resolution and appearance of new ones.

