### Eligibility criteria

2.2

To be eligible for randomization, an individual must comply with all of the following criteria:

Inclusion criteria:

Symptomatic grade II and III hemorrhoids according to Goligher classification.No other source of anal bleeding than hemorrhoids due to total colonoscopy.Written voluntary informed consent.

Exclusion criteria:

Any previous hemorrhoid surgery (including mini invasive procedures).Anal fistula.Chronic anal fissure with severe spasm of anal sphincters.Any stage colorectal cancer.Oral anticoagulants for congenital disorders of the coagulation system.Pregnancy.

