### Sample size

2.5

Considering that this is a noninferiority study, the sample size was calculated using 1-sided Blackwelder test.^[5]^ According to published data, the incidence of recurrence rate of suture ligation of the hemorrhoidal arteries with mucopexy varies from 20% to 30%.^1^,^2^,^3^,^4^ The expected incidence of recurrence rate of HD after digital detection of hemorrhoidal arteries pulsation followed by suture ligation and mucopexy is not more than 35%. The purpose of this study is to show that the outcomes of HAL-RAR procedure with digital detection of hemorrhoidal arteries is noninferior compared to HAL-RAR procedure with Doppler-guided hemorrhoidal arteries detection.

Considering that a = 0.05; the statistical power of the study is 80%; the patients are randomized into 2 groups with 1:1 allocation ratio; the noninferiority margin D = 5%, the required sample size is 204 patients (102 patients in each of the 2 groups).

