#### Allocation

2.7.1

Participants will be randomly assigned to either control or experimental group with a 1:1 allocation ratio using fixed block randomization with a computerized random number generator. All subjects will be allocated preoperatively.

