#### Statistical methods

2.8.3

An intention-to-treat analysis will be performed. Statistical analysis was carried out using IBM SPSS Statistics v23 software (IBM Corporation, US, New York), and included a comparison of categorical (Fisher exact test) and quantitative (unpaired Student *t* test) indicators in groups. The results were considered statistically significant, with a value of *P* ≤ .05.

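### The stated Fisher test makes no use of hemorrhoid grade, a baseline factor already assessed in every patient; a grade-stratified risk difference would be slightly more precise at almost no cost

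*Protocol article*

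**What the plan says.** Four places in the Protocol article bear on this.

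- Eligibility criteria (2.2): "Symptomatic grade II and III hemorrhoids according to Goligher classification" is the first inclusion criterion, so a grade must be assigned before a patient can be randomised. Section 2.7.2 adds that results of all screening procedures go into the electronic case report form.
- Allocation (2.7.1): patients are assigned 1:1, before surgery, by "fixed block randomization with a computerized random number generator". No stratification factor is named.
- Statistical methods (2.8.3): the analysis is a "comparison of categorical (Fisher exact test") and, for quantitative variables, an unpaired t test. No covariate is named.
- Discussion (3): the first limitation is that doctors often disagree on stage, for the patient and for each pile. The article concludes: "So the group might be heterogenic regarding the preoperative stage of the HD".

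The yardstick is in Sample size (2.5): "the noninferiority margin D = 5%, the required sample size is 204 patients (102 patients in each of the 2 groups").

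**The concern.** The article acknowledges that its patients may be mixed in stage, then states an analysis that cannot take stage into account. Recurrence (2.4.1) includes persistence of any initial symptom, prolapse among them, so it may plausibly depend on baseline grade. The article gives no figure for that dependence. If it exists, some of the uncertainty in the arm difference comes from chance differences in grade mix between arms, and a stratified estimate would remove that part without another patient or measurement.

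What is at stake is precision. With 102 patients per arm and a 5-point margin, a cheap reduction in the standard error is worth taking, provided its size is stated honestly.

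**Working it through.** **Inputs from the article.** n = 102 per arm and margin 5 points (2.5). The calculation is one-sided: "the sample size was calculated using 1-sided Blackwelder test", with alpha 0.05. Published recurrence "varies from 20% to 30" per cent (2.5); 30% is used below.

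**Inputs assumed, because the article does not give them.** Share of grade III q = 50% (also 20%, 30% and 70%). Recurrence gap between recorded grades d = 10, 20 or 30 points.

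The article gives no figure of its own on grade, so there is none to reproduce for this point.

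**Step 1. Unadjusted standard error.** SE = sqrt(2p(1−p)/n) = sqrt(2 × 0.30 × 0.70/102) = 6.42 points.

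**Step 2. Standard error after stratifying.** The share of outcome variance explained by grade is R = q(1−q)d²/[p(1−p)]. The stratified SE is approximately 6.42 × sqrt(1−R).

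| d (points) | R at q = 50% | SE at q = 50% | SE at q = 30% |
|---|---|---|---|
| 10 | 0.25 × 0.01/0.21 = 1.2% | 6.38 | 6.42 × sqrt(0.99) = 6.38 |
| 20 | 0.25 × 0.04/0.21 = 4.8% | 6.26 | 6.42 × sqrt(0.96) = 6.29 |
| 30 | 0.25 × 0.09/0.21 = 10.7% | 6.06 | 6.42 × sqrt(0.91) = 6.12 |

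At q = 50% the SE falls by about 0.6%, 2.4% and 5.5%.

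**Step 3. What that does to the decision (q = 50%, d = 20).** The distance from the estimate to the one-sided 95% limit falls from 1.645 × 6.42 = 10.6 to 1.645 × 6.26 = 10.3 points. Power at equal true rates, Φ(5/SE − 1.645), rises from about 19% to about 20%.

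**Step 4. How far chance imbalance can move the difference.** The SD of the between-arm difference in grade III share is sqrt(2q(1−q)/n) = sqrt(2 × 0.25/102) = 7.0 points, so its 1.96-SD limit is 13.7 points. The shift in the arm difference is d × imbalance.

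| d (points) | Shift at 1.96 SD | P(shift > 2.5 points, either direction) |
|---|---|---|
| 10 | 1.4 | 0.04% |
| 20 | 2.7 | 7.4% |
| 30 | 4.1 | 23% |

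To reach 2.5 points, half the margin, at the 1.96-SD limit, d must be at least 2.5/0.137 = 18 points at q = 50%, or 20 points at q = 30%. At d = 20 the probability is 5.1% for q = 30% or 70% and 2.6% for q = 20%. In the unfavourable direction alone, each probability is halved.

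**Step 5. This shift is already counted.** At d = 20 the 1.96-SD shift of 2.74 points sits inside a total 1.96-SE range of 1.96 × 6.417 = 12.58. Taking it out leaves sqrt(12.58² − 2.74²) = 12.27 = 1.96 × 6.26, which is the stratified SE of step 2.

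**The case against.** The case against raising this is substantial.

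- **Unstratified randomisation with an unadjusted test is valid.** This stands. Chance imbalance in grade is not bias, and the unadjusted SE includes it (step 5). A reader might infer that imbalance could by itself make noninferiority appear or disappear, or shift the result by more than half the margin. The article does not support that: it gives no grade mix and no recurrence by grade, and such a shift needs an assumed gap of about 18 points or more together with an imbalance near its 95% limit.
- **The Discussion speaks of disagreement between doctors and of the study group, not of imbalance between arms.** This also stands. A reader might infer that the authors expect the arms to differ in grade. They say only that the group might be mixed. Stratifying does not make graders agree.
- **Misgrading weakens the remedy.** True, but it does not invalidate it. A grade fixed before allocation cannot depend on the arm, so errors in it shrink the gap d between recorded grades, and with it the gain, without biasing the comparison.
- **A condensed article may leave stratification factors and covariates to the full protocol or analysis plan.** Those documents are not shown, so silence alone is not a finding. What remains is that the article does state its test, and a Fisher test on a two-by-two table cannot use grade.
- **The larger weakness is the sample size.** Agreed, and it is a separate matter. At equal rates of 20% to 35%, a 5-point margin with one-sided alpha 0.05 and 80% power needs 792 to 1126 per arm. Stratifying barely touches that.

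**Conclusion.** The point holds as a minor efficiency improvement. The stated analysis ignores a baseline factor that every patient must have assessed before allocation and that the authors themselves mention. Stratifying by it would lower the SE by about 1% to 6%, assuming half the patients are grade III, 30% overall recurrence, and a gap between grades of 10 to 30 points. None of the grade figures comes from the article. With a smaller gap, or poorly reproducible grading, the gain approaches zero.

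It should not be read as a flaw that threatens the validity of the comparison. Even at an assumed 20-point gap, an imbalance effect above 2.5 points has a probability of about 7%, counting both directions.

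**What to change.** - **Analysis.** For the primary outcome, estimate the recurrence risk difference (finger-guided minus Doppler-guided) stratified by the grade recorded at screening, by Mantel-Haenszel or stratified Miettinen-Nurminen. Compare its one-sided 95% upper limit with the 5-point margin. This also yields a quantity to set against the margin, which a Fisher P value does not.
- **Definition of the stratum.** Use the grade entered before allocation and do not revise it afterwards. Because the Discussion notes that piles may differ in stage, fix a rule for the patient-level value, for example the highest pile grade.
- **Randomisation.** If it has not started, generate the block list separately for grade II and grade III. If it has, make the analysis change alone.

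The cost is one line of analysis wording, a one-sentence stratum definition and, if used, a second list. No extra patients, visits or measurements are needed.
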